#### Stimulation functionality

- Allows for stimulation and EEG recording simultaneously
- Number of channels: up to 32 channels
- Types of Stimulation: tDCS, tACS, tRNS, sham
- Current: maximum of  $\pm$  2mA per electrode
- Current resolution: 1  $\mu$ A
- Current accuracy: 1%
- Battery-powered
- Maximum voltage:  $\pm$  15V per electrode (allows 30V of stimulation potential difference)

## 6.2 Components of the device

In terms of manufacturing, Starstim NECbox is composed of three main parts: an electronic board, a case, and a battery. The electronic board is manufactured by Lab Circuits and the assembly of the components is subcontracted to one of the main providers of Neuroelectronics, DigiProces. The case is subcontracted to a specialized company in industrial designs, called Ecceleni. Additionally, batteries are purchased at local retailers as they are standard rechargeable 3.7 V lithium ion batteries. Finally, the assembling of the mentioned parts is conducted in Neuroelectronics' factory.

Most of Starstim's electrodes are manufactured in Neuroelectronics' facilities. Pistim electrodes (Ag/AgCl) are subcontracted to Sautel and Sponstim electrodes are subcontracted to Canadian Medical Products LTD. Canadian Medical Products LTD has the Food and Drug Administration (FDA) establishment registration number: 802219. The neoprene headcap and headband manufacturing are subcontracted to a tailoring workshop in Spain, called Proline. Each electrode should be replaced after 10 hours of stimulation because the Ag/AgCl is expected to be consumed.

The electrode gel is a highly conductive and bacteriostatic gel. It is water soluble, non-staining and non-gritty. It is used for EEG monitoring electrodes and for the hybrid EEG/tCS Pistim electrodes. It is used to improve the contact between the electrode and the scalp by decreasing the impedance. The 12 ml curved syringe is used to inject either electrode gel or saline in the electrodes. With the Geltrode and the Pistim, the curved tip of the syringe should be inserted on the small hole of the electrode to inject the electrode gel into the rear-fill aperture.

NIC is the proprietary software. The software manages the basic control of the device and sends the commands to the device and receives the status and the data from the NECbox. NIC controls the Windows API which manages the Starstim-computer pairing process and data reception. Once paired, one can also intentionally revert to the unpaired state by closing the software or pairing to another device. Once the Bluetooth® connection is established, NIC can be used to direct Starstim to record EEG signals or apply neurostimulation protocols. The software does not perform the core functionalities of the device. The NECbox has an internal control that takes the control of the generation of the stimulation waveforms, the impedance control and the EEG monitoring management. The NIC software is fully created and developed in Neuroelectronics, in Spain. NIC Software is in compliance with IEC 62304: 2006. The software is classified as Class B following the IEC 62304:2006. Neuroelectronics periodically inspects their critical suppliers (according to the internal procedure GP-010 - Supplier's Evaluation) to control that their products and services conform to specified requirements.

For blinding the administrator and operator, rules will be assigned. The administrator will be the person who can create and manage the protocols. In a double blind study, the administrator will create a series of protocol templates for stimulation and give them generic names that do not provide montage related information. One protocol will refer to the real stimulation sessions, while a second protocol will correspond to the sham stimulation. The administrator will also prepare a list for the operator assigning a protocol to each subject and session (e.g. Subject01\_Session01). The operator will be responsible for selecting the appropriate protocol for the session/subject, setting up the electrodes according to the montage, checking impedances, launching it and annotating the session as needed. During the stimulation session, the operator will have no access to protocol data (currents, sham settings, EEG traces, etc.) and will remain effectively blinded.

### 6.3 Manufacturer

Neuroelectrics Barcelona S.L.U.  
[name]  
[name]

[contact]  
[contact]  
Email: [[contact]](mailto:[contact])

Neuroelectrics is an ISO 13485 and ISO 9001 certified company <http://www.neuroelectrics.com/>. Thus, their medical devices are designed and manufactured following the corresponding ISO quality management systems. Neuroelectrics complies with Quality System Regulation 21 CFR 820. Neuroelectrics manufactures all their products in a factory located in Barcelona, Spain. The factory is yearly inspected by the SGS United Kingdom Limited, Notified Body number 0120, [name]. Last year, Neuroelectrics was successfully audited on May 23, 2016. Compliance is supported by the CE Certificate number ES12/11935 Production Quality Assurance.

### 6.4 Serial number or batch label

Each device is marked using the following code: EYYYYMMDD-XX (Figure 2). Where YYYYMMDD indicated the date in the year/month/day format when the device was produced and XX is an incremental counter for the devices in the same day. The devices have also the unique MAC address at the label.

[figure not shown]

Figure 2. Starstim R32 labels

Each device will have attached a sticker providing the following information: study title (STIPED: E-StimADHD), EUDAMED number, sponsor's name (KKS Magdeburg), a unique serial number, a contact address of the local physician who is responsible for the clinical trial in case of emergencies, and a warning that the device is "only intended for clinical investigation".

### 6.5 Storage, shipping and return as well as documentation of medical devices (device accountability)

#### 6.5.1 Storage

Starstim32 must be used with normal temperature, humidity and pressure conditions:

- Temperature Range: +5 to 40 °C
- Humidity: 15 - 93 %
- Atmospheric Pressure: 700 - 1.000 hPa

The device must be stored inside the box between uses, in the following environmental conditions:

- Temperature Range: -25 to +70 °C
- Humidity: 15 - 93 %

This equipment needs to be installed and put into service in accordance to the information provided in this user manual.

### **6.5.2 Packaging**

The primary package contains the components of the Starstim in a foam box organized in a way to be also a functional box to storage the product during the rest of the life of the product. In the case of Starstim, primary and secondary packaging are the same. The packaging box is common for all the Neuroelectrics' products, and the Label identifies which product it contains. The size of the box is: 350 x 240 x 75 mm in a closed position. The primary and secondary packaging are used for the shipment and storage of other products. There has not been any damage or reported problem related to the storage or shipment. The primary and secondary package containing Starstim are compliant with IEC 60601-1:2005 and IEC 60601-1-11:2010.

For traceability purposes, the primary and secondary packaging contain a Label including the following information:

- Name and address of the manufacturer
- Product model and description
- Serial Number and Mac of the device

### **6.5.3 Documentation**

An investigator shall maintain the following accurate, complete, and current records relating to the device use in an investigation:

1. Records of receipt, use or disposition of a device that relate to:
  - The type and quantity of the device, dates of receipt, and batch numbers or code marks
  - Names of all persons who received, used, or disposed of each device
  - The number of units of the device returned to the manufacturer, repaired, or otherwise, disposed of, and the reason(s) therefore.
2. Records of each subject's case history and exposure to the device, including:
  - All relevant observations, including records concerning adverse device effects (whether anticipated or not), information and data on the condition of each subject upon entering, and during the course of, the investigation, including information about relevant previous medical history and the results of all diagnostic tests
  - A record of the exposure of each subject to the investigational device, including the date and time of each use, and any other therapy.
3. The protocol, with documents showing the dates of and reasons for each deviation from the protocol
4. Any other records that requires to be maintained by regulation or by specific requirement for a category of investigations or a particular investigation.

### **6.5.4 Return**

Upon completion of the trial, investigators are required to return to the manufacturer any remaining supply of the device or otherwise dispose of the device as the manufacturer directs. It has to be documented for each trial site.

## **6.6 Directions for use of medical devices**

All sites will be trained and supervised by personnel certified in the use of Starstim32. Relevant information conveyed during training is based and documented in the User Manual (I, II & III).

## 7 STUDY PROCESS

### 7.1 Study enrollment

#### 7.1.1 Assignment to study arm / randomisation

After definite inclusion into the study (signed informed consent), each patient will be allocated randomly to one of the two studies (**Study A** or **Study B**) and within each study to one of the two treatment conditions (anodal tDCS stimulation or sham stimulation) using a randomized block design. Each block will consist of four patients. Block randomization will be done with the electronic randomization tool BiAS for Windows (version 11, 2016; see chapter 11.2). The randomisation results will be transmitted to the center through the eCRF system in the form of the file name (file containing protocol templates for stimulation) which only reveals the assigned study (Study A or Study B, necessary to perform the specific tasks of the study), but not the treatment condition (sham or real stimulation).

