#### 5.2.3 Concomitant medication and therapy

The main aim of the proposed study is to assess the potential effect sizes tDCS can have on impaired neuropsychological performance in ADHD as a possible alternative to stimulant medication. Therefore, it is essential to obtain pre- and postintervention measures devoid of the normalizing stimulant effect. From clinical experience, families often use stimulants flexibly e.g. refrain from medication during the weekends or vacations. Moreover, a considerable number of patients do not use medication to treat their ADHD at all. Participants will be asked to refrain from stimulant use throughout the entire study, at least two weeks prior to V0. Time without stimulant treatment can vary between 7 to 15 weeks

between participants depending mostly on the time windows between screening and V0 and the beginning of the intervention. Beside stimulant treatment, concomitant neurofeedback therapy is not allowed. Other ongoing interventions such as behavior therapy or occupational therapy can be continued.

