### 7.2 Visits

#### Screening visit

1. Information of participants and their parent(s) and confirmation of consent
2. Assessment of inclusion and exclusion criteria
  - Medical and psychosocial history
  - K-SADS-PL
  - IQ test
  - Social Communication Questionnaire (SCQ)
  - Assessment of MRI criteria
  - Pregnancy test (urine test)
3. Assessment of participants' characteristics
  - Edinburgh Handedness Inventory (child)
  - Social economic status of the parent(s)
  - Pubertal Developmental Scale (child, parent)
  - Expectations and concerns towards tDCS (child/parent)
  - ADHD rating scale (parent)\*
  - Quality of Life (KIDSCREEN-27, child/parent)\*

*The last two questionnaires\* can be filled out at home and be returned at baseline.*

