**Baseline visit (Visit 0, within 4 weeks after screening)**

- Assessment of arousal, mood and motivation before and after the session (SAM, VAS, diary)
- Resting state, 64-channel EEG
- Neuropsychological performance (tasks: n-back, Flanker, CPT), 64-channel EEG
- Assessment of adverse events
- Randomization

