**Visit 1 to 10 (V1 within 4 weeks after V0)**

- Assessment of arousal, mood and motivation before and after the session (SAM, VAS, diary)
- Multichannel stimulation (sham/real) of either the dlPFC (**Study A**) or the rIFG (**Study B**) during a task
- EEG before and after the multichannel stimulation
- Assessment of adverse events during stimulation (safety questionnaire)
- Assessment of adverse events

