### 11.3.2 Analysis population

The primary analysis will be based on the intention-to-treat (ITT) set, including all randomized patients irrespective of the amount of treatment actually received. A per-protocol (PP) analysis will be performed as sensitivity analysis. All participants will be asked to participate in the end-of-treatment and follow-up assessment, even if they drop out of treatment, to minimize the number of those who are lost to follow-up. Deviations from the protocol that lead to exclusion from the PP-set will be detailed in the SAP.

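### Protocol sections 7.1.1 and 7.2 place randomisation at different points, and either allows a wait before the first stimulation whose losses stay in the ITT set

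*Combined protocol and SAP*

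**What the plan says.** Protocol section 7.1.1 ties allocation to inclusion, and the parenthesis names consent as the condition: "After definite inclusion into the study (signed informed consent), each patient will be allocated randomly to one of the two studies". In section 7.2, consent is the first item of the screening visit. The second item is headed "Assessment of inclusion and exclusion criteria" and covers the diagnostic interview, the IQ test and the pregnancy test, among others. Section 7.2 then gives "Randomization" as the last item of V0.

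The visit windows in 7.2 are "Baseline visit (Visit 0, within 4 weeks after screening" and "Visit 1 to 10 (V1 within 4 weeks after V0". Neither has a lower limit. Section 5.2.3 adds: "Participants will be asked to refrain from stimulant use throughout the entire study, at least two weeks prior to V0".

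The primary analysis uses the ITT set, "including all randomized patients irrespective of the amount of treatment actually received" (protocol 11.3.2); SAP section 5.2 agrees. The SAP's safety set requires at least one started session, so the SAP itself allows for children who are randomised and never stimulated. Section 11.2 of the protocol and the examination plan give no time point for randomisation. The flow-chart figure is not visible in the text available for this review.

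**The concern.** The two sections give different trigger points, so the moment at which a child enters the ITT set is not fixed. Either trigger opens an interval between allocation and V1 in which a child can withdraw, resume medication or become ineligible. Eligibility assessment is scheduled at screening only. A child lost in that interval has received neither tDCS nor sham but counts in the primary analysis.

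Little is gained by allocating earlier. The V0 tasks (n-back, Flanker, CPT) are the same in both studies, and the eCRF returns a stimulation file name that is first used at V1. Allocation at V1 would turn losses during the wait into pre-randomisation losses. The primary objective is an effect size, so avoidable dilution bears on it directly.

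**Working it through.** **Timing.** From the windows in 7.2:
- V0 to V1: 0 to 4 weeks. This is the wait if randomisation is at V0.
- Screening to V1: at most 4 + 4 = 8 weeks. This is the wait if randomisation is at consent.

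As a check on the lower end, section 5.2.3 says: "Time without stimulant treatment can vary between 7 to 15 weeks". Take 14 days before V0, a V0–V1 gap g, 11 days from V1 to V10 (two five-day blocks with a two-day break) and 28 days to V12:
- g = 0: (14 + 0 + 11 + 28)/7 = 7.6 weeks.
- g = 28 days: (14 + 28 + 11 + 28)/7 = 11.6 weeks.

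The stated minimum of about 7 weeks fits only a short gap, so the protocol itself expects some children to wait hardly at all.

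**The plan's own sample size.** Inputs from section 11.1: two-sided t-test, α = 0.05, d = 0.6, power 80%, 10% drop-out. The noncentral t calculation gives 44.59, rounded up to 45 per group (power 80.4%). Then 45/0.9 = 50 per arm and 100 per study. The stated figures reproduce. With all 50 per arm measured and treated, power is 84.4%.

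**Never treated, but measured at V11.** Let f be the share never stimulated, equal in both arms, with the same mean outcome whichever arm they were allocated to and an unchanged SD. Then d_eff = 0.6 × (1 − f). The documents give no f, so these values are assumptions:

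| f | d_eff | Power, 50 per arm measured | Power, 45 per arm measured |
|---|---|---|---|
| 0% | 0.600 | 84.4% | 80.4% |
| 2% | 0.588 | 82.9% | 78.8% |
| 5% | 0.570 | 80.6% | 76.2% |
| 10% | 0.540 | 76.2% | 71.7% |

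The last column applies when other drop-out also uses the full allowance.

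**Never treated and not measured.** The loss is then mainly one of precision. With d = 0.6 and 50 × (1 − f) per arm, power is 82.5% at f = 5% and 80.4% at f = 10%. The drop-out allowance is 50 − 45 = 5 per arm, so f = 10% would use all of it before any treatment is given. Imputation under MAR may also fail to reflect that these children were untreated.

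These two routes are alternatives for any one child: a measured child dilutes d, and an unmeasured child uses the allowance.

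**The case against.** The strongest reply is that this is ordinary ITT practice and the plan handles it. Untreated children are kept by declaration. All randomised patients are asked to provide the primary outcome (7.4.2.1). The per-protocol set drops anyone missing two or more sessions. Imputation is backed by mixed-model, complete-case and MNAR analyses (SAP 7.6). Randomising at the end of baseline is common, and randomisation is run centrally by IMIS/ZKS. All of this stands: keeping untreated children is not an error. What remains is that the design can create them avoidably and that two sections disagree.

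The size is also open to challenge. A shift in d of 0.01 to 0.06 is small beside a 95% interval half-width of about 1.96 × √(2/50 + 0.6²/200) = 0.40. That is fair, and it limits the weight of the point.

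Allocation before V1 also has a use: the administrator prepares the operator's list of protocols by subject and session (protocol 6.2). However, the templates are made before randomisation (7.1.2) and the file name arrives through the eCRF, so the cost is same-day preparation.

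A reader might infer more than the documents support:
- **That four to eight weeks always pass before stimulation.** The windows are upper limits, and the wait can be close to zero.
- **That ineligible children are randomised.** Section 7.1.1 also speaks of definite inclusion, and under 7.2 the screening checks come first. It would happen only if the parenthesis is followed literally, or if a child's status changes after screening.
- **That untreated children usually lack a V11 value.** Nothing supports this, and 7.4.2.1 aims at the opposite.

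**Conclusion.** The point holds as an unresolved inconsistency with a modest, avoidable cost. Sections 7.1.1 and 7.2 disagree on when randomisation occurs, and nothing visible settles it; the flow-chart might. The wait before V1 is at most 4 weeks under 7.2, and at most 8 under a literal 7.1.1.

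On an assumed 2% to 10% never treated but measured, d falls from 0.6 to 0.59–0.54 and power at 50 per arm from 84.4% to 82.9%–76.2%. Power stays above 80% at f = 5%. These figures rest on the plan's unadjusted t-test, equal shares in both arms and full measurement at V11; the planned covariate adjustment would change the absolute power. Because allocation is concealed and blinded, the expected harm is dilution or lost precision. The documents give no ground for inferring bias between arms.

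**What to change.** State one rule in 7.1.1, 7.2 and the flow-chart: allocation through the eCRF at V1, after V0 is complete and the existing eligibility criteria have been re-confirmed, and before the first stimulation. Remove the parenthesis that equates inclusion with consent. Leave the strata (center, gender) and the block length of four unchanged. A randomisation entry in the examination plan would make the rule visible.

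The cost is protocol wording and one eCRF trigger. Sites would learn the Study A or B assignment and the stimulation file name only on the day of V1, so both task and montage set-ups, and the operator's blinded protocol list, must be ready by then. If the sponsor prefers to keep allocation at V0, aligning 7.1.1 with 7.2 still removes the contradiction, but losses between V0 and V1 remain in the ITT set.

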#### 7.1.2 Blinding

Subjects will be blinded to treatment allocation for the whole duration of the trial as the sham stimulation is indistinguishable from real stimulation. The device Starstim32 (Neuroelectronics, Barcelona, Spain) allows to perform double-blind stimulation. The administrator, the person who can create and manage protocols, will create a series of protocol templates for stimulation prior to randomization and give them names that do not provide stimulation related information. The statistician creates a material file and needs to know the exact data file names of each scenario. During the stimulation session, the operator will have no access to the protocol data (currents, shamsettings) and thus remain effectively blinded.

#### 7.1.3 Unblinding

Unblinding will be done in case of the following emergencies:

- Decision of investigator: unblinding is necessary for reasons of subjects safety and for decision of further medical treatment
- A Serious Adverse Event (SAE) becomes a Suspected Unexpected Serious Adverse Reaction (SUSAR) and has to be unblinded for notification to authorities and ethics committee.

Unblinding will be performed through emergency envelopes on site, which contain information of sham or stimulation. The participant and his/her parents have to be informed about unblinding. The Sponsor has to be informed in writing about any unblinding process and the process itself has to be documented in detail on site. Unblinding leads to the exclusion of the respective participant.

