### 7.4.2 Premature end of study

#### 7.4.2.1 Withdrawal of study subject

##### Decision of study subject

Children and adolescents as well as their caregivers can refrain at any time and without providing reasons from study participation. They will be informed that their concurrent or subsequent treatment

will not be affected or compromised because of the patient's decision. All participants will be offered a final physical examination once they participated in at least one intervention session and regardless after which visit they decided to stop participation.

All randomised patients will be asked to provide their consent to be assessed for the primary outcome, in particular, those who discontinue treatment prematurely to keep missing data due to loss to follow-up at a minimum.

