## **8.8 Emergency measures**

In case, a serious adverse event occurs during or right after the stimulation, participants will be immediately transferred to emergency care at the participating site. In case of suspected relationship to medical device/treatment unblinding will be performed.

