### 5.1 Definitions of data sets

- Page 6 von 22

- (2) The participants who completed the study without any major protocol violations (see chapter 5.2) will be analyzed in the **per protocol (PP)** data set. A PP analysis includes only those participants who adhered to all important aspects of the study protocol and, thus, provides an estimate of the optimal efficacy of anodal tDCS in comparison to sham stimulation.
- (3) The **safety (SA)** data set includes all randomized subjects who started at least 1 double-blind stimulation session (stimulation visits V1 to V10 between Baseline (T2) and Post (T3), see Figure 1). It will be the main data set for the analysis of safety and tolerability of anodal tDCS stimulation. Patients will be analyzed according to the actually received treatment.

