## 5.2 Protocol violations

In general, a major protocol violation is defined as a relevant non-compliance to the study protocol that leads to exclusion of participants from the PP data set (Bhatt, 2012).

In both studies, E-StimADHD **Study A** and **Study B**, relevant protocol violations are:

(1) Protocol violations that lead to **exclusion** of the participant from the **per protocol analysis** (sham vs. verum at T3/V11):

- V0 or V11 is missing
- missing two or more of the ten stimulation sessions
- on two or more of the ten stimulation sessions, the total duration of stimulation was below 18 minutes for any reason including malfunction or incorrect use of the device
- the placement of tDCS electrodes was incorrect on two or more of the ten stimulation sessions
- stimulation medication at V0 and/or during stimulation (V1-V10) and/or at V11
- occurrence of a neurological or psychiatric disorder included in the exclusion criteria after screening
- start of participation in a clinical trial or neurofeedback after screening

(2) Further important protocol violations are **delayed visits** (e.g., due to sickness):

- time period between V1 and V10 exceeds 3 weeks
- time period between V10 and V11 is longer than 8 days

Participants with one or more protocol violations are excluded from PP analyses. The motivation is to ensure that comparisons are made between those participants only who adhered in important aspects to the study protocol.

The primary analysis will be based on the ITT set including all randomized participants. A PP analysis will be performed as sensitivity analysis. Occurring differences between both sets will be documented in the result report.

Further protocol violations regard only a subset of data:

Protocol violations relevant to the **analysis of V12**:

- V12 is missing
- the participant has been excluded from the analysis of V11

- period shorter than 4 weeks between V10 and V12
- Participant took **stimulant medication** between V11 and V12

Protocol violations relevant to the **analysis of questionnaire data**:

- questionnaires are returned more than 7 days after the respective visit

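### Protocol 7.1.3 excludes unblinded participants without saying from what; exclusion from analysis or from the study would each conflict with the rest of the plan

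*Combined protocol and SAP*

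**What the plan says.** **The rule.** Protocol 7.1.3 closes with "Unblinding leads to the exclusion of the respective participant". It names no analysis set and does not mention treatment, participation or follow-up.

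**When unblinding happens.**
- Protocol 7.1.3 allows it when the investigator decides that "unblinding is necessary for reasons of subjects safety and for decision of further medical treatment", and when a serious adverse event becomes a SUSAR.
- Protocol 8.8, on serious events during or right after stimulation, adds "In case of suspected relationship to medical device/treatment unblinding will be performed".

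**Who is analysed.**
- Protocol 11.3.2 defines the ITT set as "including all randomized patients irrespective of the amount of treatment actually received". SAP 5.2 likewise bases the primary analysis on everyone randomised.
- The safety set in SAP 5.1 "includes all randomized subjects who started at least 1 double-blind stimulation session".
- The per-protocol exclusions in SAP 5.2 do not list unblinding.

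**Who is followed.**
- Protocol 7.4.2.1 says "All randomised patients will be asked to provide their consent to be assessed for the primary outcome", with particular reference to those who stop treatment early.
- Protocol 11.3.2 extends this to the follow-up assessment.

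**Missing data.** SAP 7.6 uses multiple imputation under missing at random for the primary endpoint. Sensitivity analyses follow, including scenarios under missing not at random.

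**The concern.** Every unblinding trigger concerns the participant's safety or medical care. If unblinding then decides whether a participant is analysed or followed, the loss depends on what happened after randomisation and may depend on treatment. That matters most for safety and tolerability, which is a primary endpoint in both documents (Protocol 2.2.1, SAP 6.2). SAP 6.2 counts the number, type and severity of adverse events within it.

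The sentence is also an instruction to sites. A coordinator who has just opened an emergency envelope and reads that the participant is excluded has no reason to schedule V11 or V12. The protocol's schedule collects adverse events at both visits.

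**Working it through.** **1. The possible meanings, set against the rest of the plan**

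| Meaning of exclusion in 7.1.3 | Compared with | Result |
|---|---|---|
| From analysis | ITT set (Protocol 11.3.2, SAP 5.2); safety set (SAP 5.1) | Contradiction: neither has an exception for unblinding |
| From the study | Outcome assessment of all randomised patients (Protocol 7.4.2.1, 11.3.2) | Conflict: no V11 or V12 visit is provided for after unblinding |
| From further treatment only | The same sections | No conflict, but 7.1.3 does not say this |

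The protocol uses the word in both of the last two senses. Under the investigator's or sponsor's decision in 7.4.2.1 it means leaving the study. Under compliance in 7.4.2.1 it means leaving further treatment, and there a sentence is added asking for the primary outcome where possible. Section 7.1.3 has no such sentence.

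**2. The plan's own sample size**

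Inputs (Protocol 11.1): d = 0.6, two-sided alpha = 0.05, power 80%, 10% drop-out. The two-sample t-test (noncentral t) gives n = 44.59, rounded up to 45 per arm. Then 45 / 0.9 = 50 per arm. Both figures reproduce, and this point does not dispute them.

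**3. Effect on efficacy power**

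The documents give no unblinding rate. Assume k participants are lost from one arm, from 0 to 5, leaving 45 against 45 − k. The noncentrality is 0.6 × √[45(45 − k)/(90 − k)] on 88 − k degrees of freedom.

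| k | Noncentrality | Power |
|---|---|---|
| 0 | 0.6 × √22.50 = 2.846 | 80.4% |
| 1 | 0.6 × √22.25 = 2.830 | 79.9% |
| 3 | 0.6 × √21.72 = 2.797 | 79.0% |
| 5 | 0.6 × √21.18 = 2.761 | 77.9% |

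**4. Effect on the safety endpoint, only if exclusion means removal from analysis**

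Assume that k of 50 tDCS participants in one study have a device-related serious event, and that all k are unblinded and dropped. Intervals are exact 95%. With zero events in m participants the upper limit is 1 − 0.025^(1/m).

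| k | All retained | After removal |
|---|---|---|
| 1 | 1/50 = 2% (0.05% to 10.6%) | 0/49, upper limit 7.3% |
| 3 | 3/50 = 6% (1.3% to 16.5%) | 0/47, upper limit 7.5% |
| 5 | 5/50 = 10% (3.3% to 21.8%) | 0/45, upper limit 7.9% |

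These counts illustrate the mechanism. They are not forecasts.

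**5. If exclusion means leaving the study**

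Events already recorded stay in the data, so the table in step 4 does not apply. What is lost is the V11 accuracy score, the V12 outcomes and the adverse-event enquiry at those visits. Imputation under missing at random treats the lost V11 score as predictable from the observed data in the imputation model. A score lost because of a suspected device effect is a doubtful case for that assumption. SAP 7.6 specifies imputation for the primary endpoint only.

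**The case against.** The strongest reply is that 7.1.3 never mentions an analysis set, and that the protocol's other uses of the word concern participation or treatment. A participant can stop and still be counted in the ITT and safety sets, neither of which carves out unblinding. The request to assess all randomised patients could be read as already covering them. The SAP also plans missing-not-at-random scenarios. All of this stands, so the contradiction with the analysis sets holds under one reading only. The replies do not settle which instruction a site should follow, because 7.1.3 is specific to unblinding, unqualified and silent on further assessment.

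Three stronger readings are tempting and not supported:
- A reader might infer that safety information on these participants is lost. Serious events are entered in the eCRF log and on the SAE form (8.3.2.1) and reported within 24 hours (8.3.2.2). The text of Amendment 3 for 8.4.2.1 continues documentation of serious device effects after premature discontinuation, for at least one week after treatment or until agreed to be adequately followed up. Nothing says that collected data are deleted. These provisions cover serious events, however, and do not replace V11 and V12.
- A reader might infer that the rule selects exactly the participants with device-related serious events. Section 7.1.3 also permits unblinding for any safety or medical reason, and 8.8 concerns events during or right after stimulation.
- A reader might extend the point to the V12 violations in SAP 5.2. That section defines major violations as per-protocol exclusions, and its only V11 exclusion list is the per-protocol one, so it does not show ITT participants being dropped.

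**Conclusion.** The point holds as an unreconciled rule. Section 7.1.3 must say what the participant is excluded from. Removal from analysis contradicts the ITT and safety sets. Ending participation conflicts with the commitment to assess everyone randomised and produces safety-related missing outcomes.

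The expected effect on efficacy is small: power falls from 80.4% to 77.9% with five lost from one arm, a number assumed here. The main exposure is scheduled V11 and V12 follow-up and the analysis of the primary safety endpoint, where even a few participants matter. The safety counts in step 4 rest on assumed event numbers and on the analysis reading.

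One limit remains: the ITT item in SAP 5.1 is not readable in the text available. The conclusion relies on Protocol 11.3.2 and SAP 5.2 instead, and draws nothing from that gap.

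**What to change.** Reconcile Protocol 7.1.3 with 7.4.2.1 and 11.3.2 and with SAP 5.1 and 5.2. Suggested text for 7.1.3:

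*Unblinded participants remain in the intention-to-treat and safety sets, are still asked to attend the V11 and V12 assessments, and are excluded from the per-protocol set only.*

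Add unblinding to the per-protocol exclusions in SAP 5.2. Make both changes before database lock and before any unblinded analysis.

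This takes no position on whether an unblinded participant receives further stimulation. The sponsor must reconcile what 7.1.3 and the withdrawal rules in 7.4.2.1 say on that.

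The cost is one sentence in the protocol, handled as an amendment under 13.5.2, and one line in the SAP. The sample size stays at 50 per arm. The downside is that a few assessments made with knowledge of allocation stay in the ITT set. The per-protocol analysis, already planned as a sensitivity analysis, covers that.
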